### Exploratory subgroup and sensitivity analyses

Where feasible and supported by data availability, we will explore whether psychometric models and treatment effects vary by sex. Measurement invariance across sex will be assessed within the optimal psychometric models using established procedures. Where invariance is violated, group-specific psychometric models will be estimated, and primary and secondary analyses repeated using sex-specific scores.

To further examine the robustness of findings to potentially important sources of between-trial and clinical heterogeneity, we will attempt to conduct additional exploratory sensitivity analyses:
•Endpoint timing (week 4 vs week 6): Given that acute antipsychotic trials commonly report outcomes around week 6, but earlier endpoints (e.g., week 4) may yield different conclusions.
^
22
^ Therefore, we will, where endpoint timing can be harmonised and sample size allows, repeat analyses stratifying trials by the closest available acute endpoint (week 4 vs week 6).•Stage of illness: Where sufficiently detailed and harmonisable information is available, we will explore whether the best-fitting psychometric model(s), invariance results, and estimated treatment effects differ according to patients’ schizophrenia history (e.g., first-episode/early-phase versus multi-episode/chronic presentations, prior treatment exposure, or other trial-reported indicators of illness course).

These exploratory analyses are motivated by the clinical and methodological need to understand whether modelling choices or trial-design and population differences (such as endpoint timing or illness course) could materially influence inferences about treatment effects. All subgroup and sensitivity analyses will be clearly labelled exploratory, and interpretation will prioritise effect estimates and uncertainty, with transparent reporting of any constraints arising from limited sample sizes, inconsistent variable availability, or restricted harmonisability across trials, consistent with STROBE reporting principles.

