^ replicating and extending these to schizophrenia trials. The primary aim of the EVIDENTIAL project is to comprehensively examine the properties of the BPRS and PANSS to determine whether psychometric refinement might meaningfully alter schizophrenia symptom structure or performance, and more crucially, whether these changes might influence estimates of treatment efficacy examined in subsequent analyses. To achieve this, we have three objectives, corresponding to three research stages:
-To determine the best psychometric models for the PANSS and BPRS-To test whether psychometrically-informed scoring of PANSS/BPRS alters estimated antipsychotic effect sizes compared with conventional total score analyses-To explore whether any changes differ across symptom domains and by sex.

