^ To select the optimal model of schizophrenia, the selection process will be guided by established absolute and relative fit indices, information criteria, and internal consistency metrics, including: the Root Mean Square Error of Approximation (RMSEA; < 0.08), Standardised Root Mean Square Residual (SRMR; < 0.08), Comparative Fit Index (CFI; > 0.95), Tucker-Lewis Index (TLI; > 0.95), Akaike Information Criterion (AIC), Bayesian Information Criterion (BIC), and McDonald’s Omega (acceptable >0.70), following established practices.
^
31,
32
^ Similar to the exploratory approach, confirmatory modelling will be performed for baseline and for the primary post-baseline outcomes. For outcome (post-baseline) measurement models, we will estimate the best-fitting model in the pooled sample and then test invariance across key arm categories (placebo vs active; and where feasible across active-arm classes as defined by the standard classification, with McCutcheon’s taxonomy explored in sensitivity analyses). We will retain the best-fitting baseline and post-baseline model(s) to derive factor scores for downstream treatment-effect estimation in Stage 2.
^
33
^

Measurement invariance, i.e. metric invariance (factor loadings are equal) and scalar invariance (intercepts are equal) across sex will be assessed, and differential item functioning examined by mean, standard error, standard deviation, factor loading scores and
*r
^2^
* values. When invariance is violated, psychometrically optimized models will be examined separated by sub-group (e.g., women and men).

The outcomes of these analyses will then be used for further evaluation and discussion (descriptively) on their differences or similarities in all models and datasets. This procedure will include model structure or item functioning (i.e. dropped items, item loadings on factor). Revised sum scores based on the retained items and weighted scores will then be computed from the best performing baseline and combined outcome model for each measure. These will be used for the stage 2 analysis described in the following sections.

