### Primary analyses: Continuous outcomes

For each instrument (PANSS and BPRS), outcome symptom severity will be modelled as a function of treatment assignment, adjusting for baseline symptom severity and accounting for clustering of participants within trials via random intercepts, as per best practice RCT modelling.
^
41
^ Detached from the psychometric modelling approach (CFA, IRT, NA) in Model 1 the overall effects of antipsychotics versus placebo, using conventional scoring (i.e., original raw scores) will be estimated. Model 2 comprises a set of related models that mirror Model 1, where raw scores are replaced with abbreviated sum scores based on the results of the psychometric analysis from stage 1. In Model 3 psychometrically-informed (weighted) scores, that are derived from the abbreviated models will be established. Model 2 and 3 will be calculated for each psychometric method separately (CFA, IRT, NA). Models 4, 5 and 6 will extend Models 1, 2a-c and 3a-c, by additionally adjusting for participant level covariates:
•Model 1 (conventional scoring): Outcome is the raw total score with treatment group and baseline score as covariates and a random intercept for trial.•Model 2 (abbreviated total scores): Outcome is a simplified total score created after removing redundant items (as per relevant psychometric method) treatment group and corresponding baseline abbreviated score included as a covariates and a random intercept for trial.oModel 2a – factor analysis abbreviated total scoreoModel 2b – IRT abbreviated total scoreoModel 2c – NA abbreviated total score•Model 3 (weighted psychometric scores): Outcome is a psychometrically derived score (e.g., factor score, IRT expected score, or net score) treatment group and corresponding baseline abbreviated score included as a covariates and a random intercept for trial.oModel 3a – factor analytic weighted scoresoModel 3b – IRT weighted scoresoModel 3c – NA weighted scores (net score)•Model 4: Model 1 additionally adjusting for participant-level covariates (e.g. sex, age [where available])•Model 5a-c: Model 2a-c additionally adjusting for the same participant-level covariates•Model 6a-c: Model 3a-c additionally adjusting for the same participant-level covariates

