Effect estimates from each model will be transformed into Cohen’s d to facilitate comparison across trials and scoring approaches. The primary effect of interest is the difference between SMDs derived from those derived from conventional scoring and psychometrically-informed outcomes (i.e. Model 1 vs Models 2a-c vs Model 3a-c, and Model 4 vs 5a-c vs Model 6a-c).

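### When sex invariance fails, the plan scores women and men with different keys and does not say that the between-sex comparison stays on a common one, so that comparison can mix key with drug response.

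*Protocol article*

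**What the plan says.** The third objective, at the end of the Background, is "To explore whether any changes differ across symptom domains and by sex". The section on exploratory subgroup and sensitivity analyses widens this: "we will explore whether psychometric models and treatment effects vary by sex".

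For failed invariance there are two statements. Stage 1, under the factor analytic approaches, covers metric and scalar invariance across sex and says: "When invariance is violated, psychometrically optimized models will be examined separated by sub-group (e.g., women and men". The exploratory section adds: "Where invariance is violated, group-specific psychometric models will be estimated, and primary and secondary analyses repeated using sex-specific scores".

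The quantity compared is defined under the primary analyses: "The primary effect of interest is the difference between SMDs derived from those derived from conventional scoring and psychometrically-informed outcomes". The abbreviated score in Model 2 is described as follows: "Outcome is a simplified total score created after removing redundant items". Model 3 replaces it with weighted scores. A key can therefore differ between the sexes in its items as well as its weights.

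The article describes no step that keeps the sexes on one metric, such as partial invariance, anchor items, or each key applied to both sexes. It does not say which set of scores answers the sex question. It labels all subgroup analyses exploratory.

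**The concern.** With one common key, a difference between women and men in the SMD change reflects how the two groups responded on the same instrument. With two keys it also reflects what each instrument contains. A key that sheds items on which the drug does little raises the SMD, and a key that sheds responsive items lowers it. If women receive the first key and men the second, a sex difference appears although every item responds identically in both.

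The rule applies only when measurement has been found to differ by sex, which is when a comparison across the sexes most needs a shared scale. At stake is a named aim of the project: a reported sex difference in the effect of rescoring, or in treatment effect, could come partly or wholly from the keys.

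**Working it through.** The article gives no figure for the sex comparison, so there is none to reproduce. The check asks how large a between-sex difference can arise when none exists at item level. The inputs from the article are the 30 PANSS items in groups of 7, 7 and 16, the pooled sample of about 31,000, the omega floor of 0.70, and the benchmark of about 10-15% in the Discussion. All effects, correlations and loadings below are assumptions.

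**1. Analytic example.** Item effects are 0.45 (positive), 0.20 (negative) and 0.30 (general), identical in both sexes. Item correlations are 0.35 within and 0.18 between domains. The SMD of a sum score is (sum of item effects) / sqrt(sum of all item correlations).

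- All 30 items: 9.35 / sqrt(30 + 113.40 + 98.28) = 9.35 / 15.546 = 0.601.
- Key dropping 6 negative items: 8.15 / sqrt(24 + 98.70 + 48.60) = 8.15 / 13.088 = 0.623.
- Key dropping 4 positive items: 7.55 / sqrt(26 + 100.80 + 65.16) = 7.55 / 13.855 = 0.545.
- Ratio of the two keys: 0.623 / 0.545 = 1.14. As a difference in SMD change: (0.623 − 0.545) / 0.601 = 13% of the conventional SMD.

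That pair of keys was chosen as an extreme. Less extreme settings in the same model, as ratios of the two SMDs over 20,000 random pairs of keys:

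| Setting | 95% range of ratio |
|---|---|
| Each key drops a random 6 of 30 items | 0.92 to 1.08 or 1.09, by run |
| Keys share 5 of their 6 dropped items | 0.97 to 1.03 |
| Same items, weights with 20% random noise | 0.97 to 1.03 |
| Equal item effects, two disjoint 6-item drops | 0.97 to 1.03 |

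With equal item effects, the extreme pair itself gives 0.98.

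**2. Simulation through the planned type of model.** It used 31,000 participants in 20 trials, 7-point items, five domains with correlation 0.4 and domain effects of 0.6, 0.3, 0.5, 0.5 and 0.2. Models were baseline-adjusted, with fixed trial effects standing in for random intercepts. Structure and effects were identical in both sexes. The keys had 22 items (women) and 25 items (men). Means over 12 runs:

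| Score | Women | Men |
|---|---|---|
| Conventional total | 0.536 | 0.535 |
| Own key | 0.587 | 0.502 |
| Other sex's key | 0.503 | 0.585 |

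The women-minus-men difference in the SMD change is 0.084 (SD 0.005), and 0.084 / 0.536 = 16% of the conventional SMD. Swapping the keys reverses it. With the women's key in both sexes it is 0.001 (SD 0.006).

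The analytic version of this model gives the dependence on domain effects. With equal effects, the four keys tried change the SMD by −0.1% to −3.7%. With unequal effects the range is −6.3% to +9.3%. For random 22-item keys (8 dropped), 95% of between-key differences lie within 1.4% of the total SMD under equal effects and within 10.8% under unequal effects.

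**3. Reliability alone.** If the SMD is proportional to sqrt(omega), two keys with omega 0.85 and 0.90 differ by sqrt(0.90/0.85) − 1 = 2.9%. With 0.80 and 0.90 the figure is 6.1%. With 0.70, the plan's floor, and 0.90 it is 13.4%.

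**4. Units.** Multiplying a key by 3 leaves its SMD unchanged. Scale units are not the source of the problem.

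**The case against.** The strongest reply is that a common-key analysis is already implied. To repeat an analysis on sex-specific scores presupposes a run on pooled scores, the conventional total is common to both sexes, and the trial-level section allows sex as a moderator. No sentence says that SMDs from sex-specific scores will be set against each other. This stands as a limit: the rule adds a conditional second analysis and does not replace the first. The gap is that the plan does not say which one carries the sex comparison.

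A second reply is that the scoring key is itself the exposure under study. If the best keys differ by sex and rescoring therefore moves the SMDs differently, that is part of the answer to Objective 3. This also stands in part. The result then describes the keys, and it misleads only if read as a sex difference in drug response, which the exploratory section also asks about.

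Third, the largest figures come from chosen keys. Identical structure in a large sample should yield similar keys, and failed metric or scalar invariance need not change which items are kept. That is right, and the low end of the range is as plausible as the high end.

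Two stronger readings are tempting. A reader might infer that in so large a sample a significance test would declare invariance violated for trivial departures. The article names no such test and refers to established procedures, so this is unsupported. A reader might also infer that sex-specific scores would enter one pooled model on different scales. The article does not say so, and Cohen's d removes pure differences in units.

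The exploratory label warns against over-reading chance findings, but does not remove a systematic effect of the keys.

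**Conclusion.** The point holds in a limited form. When invariance fails, the plan's only stated response is sex-specific scoring, and a between-sex contrast on such scores mixes retained items, weights and reliability with drug response. Randomised contrasts within each sex and the primary pooled result are untouched.

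The direction of the argument needs only that the keys differ in a way that matters for the SMD. The size rests on assumed effects, correlations and loadings:

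- about 3% (3.6% at most between the keys tried) when keys overlap heavily or drug effects are equal across domains;
- within about 8-9% for random six-item drops;
- about 14% (as a ratio) to 16% (of the conventional SMD) when keys drop different domains and drug effects are unequal.

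Only the last reaches the upper part of the study's 10-15% benchmark. The documents do not support a claim that any sex difference found will be an artefact. They do support fixing the basis of the comparison in advance, because it serves a named aim and costs little.

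**What to change.** State that the sex comparison rests on one common key, or on a partial-invariance model that frees only the non-invariant items. Estimate it as a within-trial treatment-by-sex contrast of the SMD change.

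Where sex-specific keys are derived, apply each key to both sexes. Differences between keys within one sex then show the effect of the key, and differences between sexes on one key show response. Otherwise report sex-specific scores within sex only, as a sensitivity analysis.

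The cost is a few sentences and one more multi-group model. A common key is not free of bias when non-invariance is real, so show the common-key and partial-invariance results side by side.

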### Setting, participants and eligibility criteria

This study is open to randomized controlled multi-arm trials (Phase II-IV) comparing the effects of pharmacological treatments with antipsychotics to placebo (primary outcome) or any comparator (sensitivity analysis). Individual trial size is not an eligibility criterion. Eligible trials will include adult participants diagnosed with schizophrenia, schizoaffective or schizophreniform disorders. Trials must include PANSS and/or BPRS individual participant data at baseline and outcome. Studies meeting the criteria described in
Table 1 have been requested from
vivli.org (Vivli) and
yoda.yale.edu (YODA Project). Requested studies from the YODA Project are solely sponsored by Johnson & Johnson. In addition, Vivli provides data from the following sponsors: Abbott, AbbVie, Janssen, Johnson & Johnson, Lilly, Otsuka. Previous data checks suggests that we should expect to obtain a pooled sample of ~31 000 participants from 77 studies provided on the Vivli platform (
Table 2).

**Table 1. T1:** Inclusion/exclusion criteria for selecting trials and participant data.

Variable	Inclusion criteria
Study Type	Randomized controlled multi-arm trial
Data Type	Individual Participant Data
Phase	II, IIa, IIb, III, IIIa, IIIb, and IV
Population/Diagnostic Criteria	Participants with Schizophrenia Spectrum Disorders, aged 18 years and older
Treatment	Antipsychotic medication
Comparator	*Placebo* (to establish efficacy) *Active Comparator* (to establish baseline psychometric model)
Active Comparator	*Primary* (standard) *:* first-generation vs second-generation antipsychotics (optionally adding D2 partial agonists as a third category where feasible). *Exploratory:* receptor-based taxonomy as proposed by McCutcheon et al. ^ 21 ^
Outcome	Positive and Negative Syndrome Scale (PANSS) and/or Brief Psychiatric Rating Scale (BPRS)
Covariates	Sex (if available: Age)
Moderator Variable	Sex Stage of illness (sensitivity analysis)
Timing of Outcome Assessment	6 weeks, as per Younis et al. ^ 22 ^/ *4 weeks for sensitivity analysis*

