	**Exclusion Criteria**
	All studies outside of the above parameters

**Table 2. T2:** Expected Sample.

Database One:		https://yoda.yale.edu/ (YODA Project)
Number of studies requested	-	62
Number of studies by sponsor		
*Janssen*	-	26
*Johnson & Johnson*	-	36

Database Two:		www.vivli.org (Vivli)
Number of studies requested	-	77 (62 are overlapping with YODA)
Number of studies by sponsor		
*Abbott*	-	1
*AbbVie*	-	1
*Lilly*	-	9
*Janssen*	-	26
*Johnson & Johnson*	-	36
*Otsuka Pharmaceuticals*	-	4

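### The exploratory endpoint-timing analysis compares week-4 trials with week-6 trials, not two visits in the same trials, so timing is mixed with trial differences

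*Protocol article*

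**What the plan says.** The protocol article, under Exploratory subgroup and sensitivity analyses, motivates the endpoint-timing bullet by noting that "earlier endpoints (e.g., week 4) may yield different conclusions". The method is to "repeat analyses stratifying trials by the closest available acute endpoint (week 4 vs week 6"), to be done "where endpoint timing can be harmonised and sample size allows". The set of analyses is meant to examine the "robustness of findings to potentially important sources of between-trial and clinical heterogeneity". The closing paragraph of that section lists endpoint timing among "trial-design and population differences (such as endpoint timing or illness course") and adds that "All subgroup and sensitivity analyses will be clearly labelled exploratory".

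In Table 1 the row for timing of outcome assessment gives 6 weeks and then "4 weeks for sensitivity analysis". It does not say whether this means the week-4 visit of the same trials or a separate set of trials. The exclusion row reads "All studies outside of the above parameters". Stage 1 also places the combined outcome at 6 weeks.

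The section on trial-level analyses defines the trial-level effect of interest as the psychometric SMD minus the conventional SMD, computed within each trial. The article does not say how many trials hold a week-4 rating, a week-6 rating or both.

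**The concern.** The question in the bullet is about time: would the answer differ if outcome were read at week 4? The stated method makes the trial the unit that is stratified. A trial has one closest endpoint, so no trial contributes to both sides. Randomisation protects the comparison of arms inside a trial, but not a comparison of one set of trials with another. The Limitations section itself accepts that the trials may vary in follow-up timing, inclusion criteria and data completeness. A difference between strata could therefore come from timing, from trial mix or from both, and similar strata could hide a timing effect offset by trial mix.

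At stake is what the result can be used for. The section says these analyses are there to show whether such features could materially influence inference about treatment effects. As written, the analysis describes two groups of trials and does not isolate timing.

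**Working it through.** **1. The two contrasts.** Let δ be the effect of reading outcome at week 6 instead of week 4, and b the difference in true effect between the two sets of trials for all other reasons.
- Trials stratified by closest endpoint: expected difference = δ + b.
- Week 6 minus week 4 within trials that hold both ratings: expected difference = δ in those trials; b drops out.

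This step needs no figure from outside the document.

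**2. How much of b reaches each quantity.** The document gives no value for b, so take b = 0.10 SMD as an illustration.
- Treatment SMD under either scoring: all of it, 0.10.
- Psychometric minus conventional SMD: trial differences that move both scores alike largely cancel. If refinement multiplies the effect by 1 + p, with p = 0.10 to 0.15 (the range in the Discussion), the difference between scorings is p × SMD. A gap of 0.10 in the conventional SMD then gives 0.10 × 0.10 = 0.010 to 0.15 × 0.10 = 0.015. The proportional form is an assumption.

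**3. Precision.** The plan states no standard error or trial count for this analysis, so there is no figure to reproduce.

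From the document: about 31 000 participants in 77 studies, or 31 000/77 ≈ 403 per study. With 1:1 arms (assumed), the sampling variance of a trial's SMD is v = 4/403 ≈ 0.0099.

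Assumed: K = 30 trials; f = share of trials in the week-4 stratum, so K4 = fK and K6 = (1 − f)K; h = share of week-6 trials that also hold a week-4 rating; r = correlation between a trial's two SMD estimates; τ = between-trial SD of the true SMD; ρ = correlation between true week-4 and week-6 effects.

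- Stratified: Var_B = (v + τ²)(1/K4 + 1/K6)
- Within trial: Var_W = [2v(1 − r) + 2τ²(1 − ρ)]/(h·K6)

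Worked case, f = 0.3, h = 0.8, r = 0.8, τ = 0.1, ρ = 0.9 (K4 = 9, K6 = 21):
- Var_B = (0.0099 + 0.01)(1/9 + 1/21) ≈ 0.00316, SE 0.056
- Var_W = (0.0040 + 0.0020)/16.8 ≈ 0.00036, SE 0.019
- Ratio ≈ 8.9

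| f | h | r | τ | ρ | SE stratified | SE within trial | Variance ratio |
|---|---|---|---|---|---|---|---|
| 0.3 | 0.8 | 0.8 | 0.1 | 0.9 | 0.056 | 0.019 | 8.9 |
| 0.5 | 1.0 | 0.8 | 0.1 | 0.9 | 0.052 | 0.020 | 6.7 |
| 0.3 | 0.8 | 0.7 | 0 | – | 0.040 | 0.019 | 4.4 |
| 0.5 | 0.5 | 0.5 | 0 | – | 0.036 | 0.036 | 1.0 |
| 0.5 | 0.3 | 0.5 | 0 | – | 0.036 | 0.047 | 0.6 |

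Over a grid of 576 settings (f 0.1–0.5, h 0.3–1, r 0.5–0.9, τ 0–0.2, ρ 0.8–1) the ratio runs from 0.6 to 251, with median 7.5. It exceeds 2 in 91% of settings, which is a share of assumed settings and not a probability.

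With τ = 0 the ratio reduces to h/[2f(1 − r)], so it exceeds 2 only if h > 4f(1 − r). That needs h > 0.24 at f = 0.3 and r = 0.8, needs h > 0.60 at f = 0.5 and r = 0.7, and cannot happen at f = 0.5 and r = 0.5.

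For the psychometric-minus-conventional difference, with τ = 0:
- f = 0.3, h = 0.8, r = 0.3: 0.8/(2 × 0.3 × 0.7) = 1.9
- f = 0.5, h = 1, r = 0.5: 1/(2 × 0.5 × 0.5) = 2.0
- f = 0.3, h = 0.8, r = 0.7: 0.8/(2 × 0.3 × 0.3) = 4.4

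**The case against.** The protocol claims little for this analysis. It is conditional, labelled exploratory and framed as a check on between-trial heterogeneity. Repeating analyses by a trial-design feature fits that frame. No test between strata is announced, and nothing says a difference will be read as causal. The main quantity of the study is paired within trial, which removes much of the trial mix. Eligibility requires ratings only at baseline and outcome, so a week-4 rating may be missing from many week-6 trials, and stratifying is the only way to use trials that stop at week 4. All of this stands, and it limits the consequence. It does not make the stratified result an answer to the bullet's own question.

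Three stronger readings are tempting, and the document does not support them.
- A reader might infer that stratifying wastes most of the precision. With between-trial variance alone, twice as many week-6 as week-4 trials and a week-4 rating in every week-6 trial, the variance ratio is 3/[2(1 − ρ)], or 7.5 at ρ = 0.8 and 15 at ρ = 0.9. That omits within-trial sampling variance (0.0099, about equal to τ² at τ = 0.1) and assumes complete week-4 data. With τ = 0.1, ρ = 0.9, 15 week-4 and 30 week-6 trials, half of the latter holding both ratings and r = 0.5, the ratio is about 2.5.
- A reader might infer that Table 1 contradicts the sensitivity section by excluding week-4 trials. The timing row itself names 4 weeks for sensitivity analysis, so this is an ambiguity and not a contradiction.
- A reader might infer that week-4 trials are known to differ in drug, sponsor, period or placebo response. The document does not say so; it says only that trials may vary.

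**Conclusion.** The concern holds in a limited form. By its wording, the endpoint-timing analysis compares different trials, so it cannot separate timing from trial mix, and Table 1 does not settle whether a same-trial rerun was intended. The conclusion on confounding rests on the text alone. Its size is unknown: trial-mix differences pass in full into contrasts of treatment SMDs and only in part into the difference between scorings. A within-trial comparison is probably more precise, but the gain depends on visit availability and correlations that the article does not give, so no single factor should be quoted. The change is worth making because it is cheap and answers the stated question. The analysis is exploratory, and no primary result depends on it.

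**What to change.** Reword the endpoint-timing bullet as follows.
- In trials that hold both a week-4 and a week-6 rating, estimate the treatment SMDs and the difference between scorings at each visit with the same scoring key, and summarise the within-trial week-6 minus week-4 contrast.
- Report how many trials qualify.
- Keep the trial-stratified result, including week-4-only trials, as a descriptive supplement, with a note that the strata may differ in more than timing.
- Align the timing row of Table 1 with this wording.

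The cost is a few lines of text and one further run, provided the week-4 ratings are in the data supplied. There are two downsides. Week-4-only trials do not enter the contrast. Limiting it to participants rated at both visits would exclude those who drop out between them, so missing week-6 ratings should be handled as in the main analysis.
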